## Abstract

**Background:**

Over the past decade, the prevalence of stunting has been close to 37% in children aged <5 years in Indonesia. The Baduta program, a multicomponent package of interventions developed by the Global Alliance for Improved Nutrition, aims to improve maternal and infant nutrition in Indonesia.

**Objective:**

This study aims to assess the impact of the Baduta program, a package of health system strengthening and behavior change interventions, compared with the standard village health services on maternal and child nutrition.

**Methods:**

The impact evaluation uses a cluster randomized controlled trial design with 2 outcome assessments. The first uses cross-sectional surveys of mothers of children aged 0-23 months and pregnant women before and after the interventions. The second is a cohort study of pregnant women followed until their child is 18 months from a subset of clusters. We will also conduct a process evaluation guided by the program impact pathway to assess coverage, fidelity, and acceptance. The study will be conducted in the Malang and Sidoarjo districts of East Java, Indonesia. The unit of randomization is the subdistricts. As random allocation of interventions to only 6 subdistricts is feasible, we will use constrained randomization to ensure balance of baseline covariates. The first intervention will be health system strengthening, including the Baby-Friendly Hospital Initiative, and training on counseling for appropriate infant and young child feeding (IYCF). The second intervention will be nutrition behavior change that includes *Emo-Demos*; a national television (TV) advertising campaign; local screening TV spots; a free, text message service; and promotion of low-cost water filters and hygiene practices. The primary study outcome is child stunting (low length-for-age), and secondary outcomes include length-for-age Z scores, wasting (low weight-for-length), anemia, child morbidity, IYCF indicators, and maternal and child nutrient intakes. The sample size for each cross-sectional survey is 1400 mothers and their children aged <2 years and 200 pregnant women in each treatment group. The cohort evaluation requires a sample size of 340 mother-infant pairs in each treatment group. We will seek *Gatekeeper* consent and written informed consent from the participants. The intention-to-treat principle will guide our data analysis, and we will apply Consolidated Standards of Reporting Trials guidelines for clustered randomized trials in the analysis.

**Results:**

In February 2015, we conducted a baseline cross-sectional survey on 2435 women with children aged <2 years and 409 pregnant women. In February 2017, we conducted an end-line survey on 2740 mothers with children aged <2 years and 642 pregnant women. The cohort evaluation began in February 2015, with 729 pregnant women, and was completed in December 2016.

**Conclusions:**

The results of the program evaluation will help guide policies to support effective packages of behavior change interventions to prevent child stunting in Indonesia.

**International Registered Report Identifier (IRRID):**

RR1-10.2196/18521

## Introduction

### Background

Over the past decade in Indonesia, there has been little change in child stunting, with the national prevalence of stunting estimated as 37% of children aged under 5 years [1,2]. This high level of growth failure has profound adverse consequences for the physical and economic development of affected children, their communities, and the country overall [3-7]. Growth faltering among Indonesian children starts in utero and is associated with low maternal height and poor nutritional status [8-15]. Among children in Indonesia, as elsewhere, 2 major determinants—undernutrition and infections—broadly account for postnatal deterioration in growth [10,15-20]. In studies examining risk factors for child stunting in Indonesia, lower maternal education and household wealth, including lower expenditure on foods from animal sources, are associated with a higher prevalence of child stunting [15,18,19,21].

Presidential Decree Number 42/2013 on The National Movement for the Acceleration of Nutrition Improvement prioritized the improvement of nutritional status in the first 1000 days of life, with the stunting of children aged <5 years as a key indicator. The decree addresses 4 main strategies. The first is to make nutritional improvements as the mainstream of the development plan. The second is building capacity and increasing human resource competence to respond to nutritional needs in all sectors. The third is to promote effective evidence-based interventions to improve nutrition. The fourth is increasing community participation in nutrition programs. The Government of Indonesia prioritized stunting reduction as part of the Ministry of Health Strategic Plan 2015-2019 and aimed to reduce the prevalence of stunting among children aged <2 years from 33% in 2013 to 28% in 2019 [22].

In Indonesia, the public health system is decentralized and is the responsibility of the district and municipal governments. They manage health services through the District Health Office and deliver primary health care services through community health centers (*Puskesmas*). Civil society also actively participates in the health sector through a community initiative called the integrated village health post (*Posyandu).* It consists of community volunteers (health cadres), trained by village midwives, or other community health center staff. The health cadres assist with preventive health services, including nutrition education to pregnant women and caregivers of children aged 0-59 months.

In 2014, the Ministry of Health requested the Global Alliance for Improved Nutrition (GAIN) to support the Malang and Sidoarjo districts in East Java to reduce child stunting. Subsequently, GAIN initiated the *Baduta* (means children aged <2 years in Indonesian) program with funding from the Ministry of Foreign Affairs of the Netherlands and in collaboration with Save the Children, Paramitra Foundation, and PT Holland for water (Nazava). The experience and recommendations generated through the Baduta program will inform on efforts to improve nutrition and prevent stunting nationally in Indonesia. GAIN invited the University of Sydney, in collaboration with the Centre for Health Research, Universitas Indonesia, and the London School Hygiene and Tropical Medicine to conduct a comprehensive theory-driven evaluation designed to learn about the factors affecting program delivery and the achievement of the impact of the interventions [23,24]. This paper describes the study protocol for the impact and process evaluations of the Baduta program.

### Objectives

The Baduta study aims to assess the impact of a package of health system strengthening and behavior change interventions on maternal and child nutritional status compared with the standard, integrated village health post services. The primary outcome in the cross-sectional evaluation will be the prevalence of low length-for-age (<-2 Z scores) in children aged <2 years in each treatment group, whereas in the cohort evaluation, it will be the mean length-for-age Z scores in each treatment group. The secondary outcomes will include mean length-for-age Z scores, the prevalence of low weight-for-length (<-2 Z scores), child anemia (hemoglobin [Hb] <11 g/dL), indicators of infant and young child feeding (IYCF) practices, maternal and infant dietary intake, and use of iron and folic acid supplements by pregnant women.

### Hypotheses

#### Primary Hypothesis

A package of behavior change interventions and health system strengthening activities delivered to a rural population in East Java, Indonesia, over 18 months will improve women’s diet and iron supplementation in pregnancy, breastfeeding, and complementary feeding practices; promote hygienic food preparation; and promote use of clean drinking water. The interventions will reduce the prevalence of stunting (length-for-age Z score <-2 Z) in children aged 0 to 23 months by 6% (35% in the control group to 28.9% in the intervention group) as assessed in cross-sectional surveys, compared with areas with only the routine integrated village health post services.

#### Secondary Hypotheses

The interventions will (1) increase mean length-for-age Z scores, mean weight-for-age Z scores, and mean weight-for-length Z scores at 18 months in the cohort of children followed up longitudinally; (2) decrease the prevalence of low weight-for-age and low weight-for-length in baseline and end-line cross-sectional surveys; (3) decrease the number of children ill with diarrhea, acute respiratory illness, or fever in both cross-sectional and cohort assessments; (4) decrease the prevalence of anemia in pregnant women and children aged <2 years; (5) increase women’s knowledge about appropriate breastfeeding practices; (6) increase median duration of exclusive breastfeeding and the percentage of women exclusively breastfeeding at 6 months and age-appropriate breastfeeding in children aged 0 to 23 months; (7) increase women’s knowledge about appropriate complementary feeding including snacks; (8) decrease the percentage of children aged <2 years receiving snacks; (9) increase the percentage of children consuming ≥4 food groups at ages 6-8, 9-11, and 12-23 months in the end-line cross-sectional assessment and ages 7, 10 and, 17 months in children followed up in the cohort assessment; and (10) increase nutrient intakes, nutrient density, and dietary adequacy for children aged 6-23 months.

## Methods

### Study Design

The study is a probability impact evaluation [25] using a cluster randomized controlled trial with 2 parallel treatment arms. The design uses a superiority hypothesis, having one-to-one allocation of the treatments, 2 types of outcome assessments, and a process evaluation (Figure 1).

**Figure 1 figure1:**
[figure not shown]
Diagram of the study design for the impact evaluation. IYCF: infant and young child feeding.

#### Cross-Sectional Survey Assessment

The first assessment approach will use repeated cross-sectional surveys of mothers of children aged 0-23 months and pregnant women at baseline before interventions commence and 2 years later at the end line, which is the best approach to assess the impact of the intervention on the stunting prevalence in the study population (population-level impact) [26]. In the cross-sectional surveys, we will collect information on socioeconomic and demographic characteristics, infant feeding practices including intentions of the mother to breastfeed and mother’s self-efficacy with breastfeeding, child morbidity reported by mother/caregiver, contact with the health system and exposure to the interventions, maternal and child anthropometry, and maternal and child hemoglobin. We will assess the impact by comparing the change in the prevalence of key indicators between the treatment groups in children aged <2 years and pregnant women.

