### Evaluation Outcomes

#### Primary Outcomes

The primary outcome for the cross-sectional evaluation is the difference in the percentage of stunted (length-for-age<–2 Z scores) children aged 0-23 months between the intervention and the comparison groups at the baseline and end-line surveys. For the cohort evaluation, the primary outcome is the difference in the mean length-for-age Z scores between the intervention and the comparison groups every 3 months from birth to 18 months, as measured in the follow-up assessments.

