### Sampling Design and Sample Size

#### Sample Size

We estimated the targeted sample size for the study using the following assumptions: (1) in the 51 subdistricts in the Malang and Sidoarjo districts, there is a total population of approximately 4.4 million, with an average of approximately 86,000 per subdistrict; (2) assuming a crude birth rate of 17 per 1000 population per annum, 5% refuse, and 10% data losses, each subdistrict cluster would yield an average of 620 live births over 6 months; (3) an expected prevalence of stunting for children aged 0-23 months of 35% in the control clusters (based on unpublished survey data from Brebes, West Java, and Indonesian DHS data); (4) 80% power and 5% 2-sided alpha, and 1:1 ratio of interventions (subdistricts with and without the Baduta program) allocated; (5) design effect of 1.5 (lower than reported for the 2011 Indonesia DHS survey because of larger sized clusters); and (6) expected percentage point difference in the prevalence of stunting (0-23 months) between the intervention groups of 6% (35.0% in the control to 28.9% in the intervention group). (This is a relative reduction of 17%, which is lower than the 29% reduction in stunting reported in a recent meta-analysis [47] of education interventions to improve complementary feeding.)

A standard formula using established methods [48] for comparison of proportions to calculate the number of subjects required per intervention arm to test H_0_: *π*_0_=*π*_1_ is as follows:

where *z_α_*_/2_ and *z_β_* are standard normal distribution values for upper tail probabilities of *α*/2 and *β,* respectively, *π*_0_ is the proportion in control, *π*_1_ is the expected proportion in intervention, *m* is the number of individuals per cluster, and *ρ* is the intracluster correlation coefficient.

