Based on this calculation, the sample size required is 1392 mother-infant dyads from each group of 6 subdistrict clusters or approximately 232 mother-infant dyads per subdistrict cluster. We will round this up to 2800 mother-infant dyads per cross-sectional survey or 234 per subdistrict cluster. This sample size will provide 80% power assuming a Z score SD of 0.975 and 5% level of significance to detect a 0.15 Z score difference in height-for-age Z scores [49] between the intervention and the control groups in the end-line survey. Therefore, for the cross-sectional evaluation, we will select 2800 mothers of children aged 0-23 months and an additional 400 pregnant women from 12 subdistricts within the Sidoarjo and Malang districts.

For the cohort evaluation, to detect a difference in mean length-for-age Z score between the experimental and control groups at an end line of 0.35 Z score [50], assuming 80% power and 5% level of significance, with a design effect of 1.5 (see above), we will require a sample size of 272 mother-infant pairs in each of the intervention and comparison groups. Assuming a dropout rate of 25%, we need to recruit 680 mother-infant pairs (56-57 per subdistrict cluster).

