### Statistical Methods

The intention-to-treat principle will guide our data analysis, and we will include data from all participants even if they do not participate in all interventions. We will apply the guidelines of the Consolidated Standards of Reporting Trials statement for clustered randomized trials in the analysis and presentation of the results. We will conduct analyses at the woman or infant level adjusted for cluster randomization. Initially, we will assess the effectiveness of randomization by comparing potential confounding factors in both treatment groups. We will apply statistical tests with χ^2^ tests for categorical variables and an adjusted Wald test or the Fisher exact test for continuous variables to assess for any significant difference between treatment groups. *P* values <.05 will be considered to indicate a statistically significant difference between the groups. For selected dietary analyses of continuous variables, we will use the nonparametric rank order statistic, Somers’ D [51] (corresponding to rank-sum tests), as it can adjust for the cluster sampling design.

We will calculate frequency and percent distributions for categorical variables and mean and SD or median and interquartile range for continuous variables. We will characterize the dietary intake by age group, breastfeeding status (for infants aged 12-23 months), and intervention and comparison groups. We will generate medians and interquartile ranges for dietary intake distributions that are not normally distributed. We will plot the frequency distribution of IYCF practices by child age. We will also plot the frequency distribution of Z score indices (Z score curves) in 0.25 Z score intervals using a Lowes function to smooth the curves, and we will compare these distributions with the growth standard distribution. We will repeat these plots broken down by treatment groups.

For the cross-sectional evaluation, the primary analyses will compare the prevalence of stunting (low length-for-age<–2 Z score) and the 95% confidence intervals in each treatment group adjusted for clustering and any imbalanced baseline characteristics.

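### The protocol says impact will be judged by comparing change between arms, but the sample size and the named primary analysis fit only a single-time comparison; a change analysis would have about 52–69% power, not 80%

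*Protocol article*

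**What the plan says.** Four places in the protocol article bear on the cross-sectional primary comparison.

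- **Study Design, Cross-Sectional Survey Assessment:** "We will assess the impact by comparing the change in the prevalence of key indicators between the treatment groups". With one survey before and one after the interventions, this is a difference-in-differences.
- **Primary Outcomes:** the outcome is the difference in the percentage of stunted children "between the intervention and the comparison groups at the baseline and end-line surveys". Two surveys are named, and no rule says how they combine into one contrast.
- **Statistical Methods:** the primary analyses compare stunting prevalence "in each treatment group adjusted for clustering and any imbalanced baseline characteristics". There is no change or survey-by-arm term, and the survey is not named.
- **Sample Size:** the formula is a "comparison of proportions to calculate the number of subjects required per intervention arm to test" equality of two proportions, with "35.0% in the control to 28.9% in the intervention group" and "80% power and 5% 2-sided alpha, and 1:1 ratio of interventions". The companion power statement for Z scores concerns a difference "between the intervention and the control groups in the end-line survey".

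The Primary Hypothesis uses the same two percentages, control against intervention.

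**The concern.** The two surveys draw separate samples of children, so a comparison of change carries the sampling error of both. Subtracting baseline removes only the part of the subdistrict effect that persists between surveys. At the plan's design effect that part is small, so subtraction adds more variance than it removes. If the Study Design sentence governs, the primary comparison is less precise than the one that was sized, and the stated 80% power does not apply to it.

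The two contrasts can also give different estimates and P values in the same data. With 12 subdistricts a chance baseline difference in stunting is plausible: the constrained randomization balances underweight and four other covariates, but not stunting. The document should therefore say which contrast carries the primary conclusion. A baseline difference precedes the interventions and cannot itself measure their effect, so naming the baseline survey in the outcome definition adds to the uncertainty.

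**Working it through.** **Inputs from the Sample Size section.** Proportions 0.350 and 0.289 (difference 0.061); two-sided alpha 5%; power 80%; design effect 1.5; 1392 per arm stated, rounded to 1400 per arm (2800 per survey); 6 subdistricts per arm. The implied intracluster correlation is (1.5 − 1)/(232 − 1) = 0.0022.

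**Step 1: reproduce the stated sample size.** For two proportions at one time, with mean proportion 0.3195:

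n = [1.96·√(2·0.3195·0.6805) + 0.8416·√(0.35·0.65 + 0.289·0.711)]² / 0.061² = 916.05, rounded up to 917.

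917 × 1.5 = 1375.5, about 1% below the stated 1392. The unpooled variant gives 1370 and the continuity-corrected one 1424. The stated figure is thus a single-time, two-group calculation with no second survey in it.

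**Step 2: power of the end-line comparison.** Let u = (0.2275 + 0.2055)/1400 = 0.000309. With c = 0.5 as the clustering part of the design effect:

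- Variance = u(1 + c); SE = √(1.5 × 0.000309) = 0.0215
- 0.061/0.0215 = 2.83; power = Φ(2.83 − 1.96) = 81%

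**Step 3: power of the comparison of change.** Let r be the correlation between a subdistrict's effects in the two surveys. The document does not give r, so its full range is shown. Baseline variance is set equal to end-line variance.

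Variance = 2u[1 + c(1 − r)]

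| r | SE | 0.061/SE | Power, normal | Power, t on 10 df |
|---|---|---|---|---|
| 0 | 0.0305 | 2.00 | 52% | 44% |
| 0.5 | 0.0278 | 2.19 | 59% | 51% |
| 0.8 | 0.0261 | 2.34 | 65% | 56% |
| 1 | 0.0249 | 2.45 | 69% | 60% |

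On the same t reference, the end-line comparison has about 72%. Setting baseline prevalence at 35% in both arms changes the normal-quantile range only to 51–68%.

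**Step 4: can r close the gap?** Change is as precise as end line when 2[1 + c(1 − r)] = 1 + c, that is r = (1 + c)/(2c). At c = 0.5 this is 1.5, which is impossible. With baseline at 35% in both arms, 80% power for change needs about 2810 per arm per survey at r = 0, or 1873 at r = 1.

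**Step 5: achieved numbers.** With the reported sizes (baseline 1236 and 1199; end line 1383 and 1357) and normal quantiles, the comparison of change has about 48% to 64%. End line has about 80%, taking 1357 per arm.

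**Step 6: is adjustment for subdistrict baseline prevalence a free gain?** Cluster-level analyses were simulated (12 clusters, normal cluster means, t reference, 20,000 runs, no allowance for the constrained randomization). At design effect 1.5, adjusted end line has 67% at r = 0, rising to 72% at r = 1, against about 72% unadjusted. The slope must be estimated from 12 points, and that costs up to about 5 points. At an assumed intracluster correlation of 0.01, which is not in the document, the adjusted analysis has 37–62% against about 41% unadjusted.

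**The case against.** The Study Design sentence is an overview about key indicators and does not mention a primary analysis. Statistical Methods is the only section that names the primary analyses for this evaluation, and it agrees with the hypothesis and the sizing. This stands: a reader might infer that the primary analysis is formally specified in two rival ways, but the text does not go that far. The contradiction nevertheless reaches stunting, because the same paragraph presents the repeated surveys as the way to assess impact on stunting prevalence. Statistical Methods also never says end line; that has to be inferred.

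A reader might also infer that the contrast will be picked after the data are seen. This cannot be shown, since the statistical analysis plan is not at hand and the article is a condensed account. Nor do the contrasts target different effects: under randomization the expected baseline difference is zero, so they differ in precision and in the realized estimate.

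Two further limits stand. On a t reference the end-line comparison also falls below 80%, so the change analysis is not alone in missing it. And the precision loss from subtracting baseline belongs to the plan's small implied correlation. At an assumed 0.01 (c = 2.32), change beats unadjusted end line once r exceeds 3.32/4.64 = 0.72.

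**Conclusion.** The point holds as an inconsistency in wording with a measurable consequence. The overview sentence describes a comparison of change and the outcome definition names both surveys, while the sample size and the named primary analysis fit only a single-time comparison. At the plan's design effect, power is about 81% for end line and 52–69% for change with normal quantiles, or about 72% and 44–60% with 10 degrees of freedom. The ranges rest on the plan's 6.1-point effect, 1400 per arm in each survey, equal variance at the two surveys, and an assumed between-survey correlation anywhere from 0 to 1. No value in that range restores 80%.

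It is tempting to add that adjusting for subdistrict baseline stunting would recover power. At the plan's own design effect it does not, and a benefit requires a larger intracluster correlation and between-survey correlation than the plan implies or states. The grade is should-fix: the named analysis matches the sizing, so aligning the other statements resolves it.

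**What to change.** - In Cross-Sectional Survey Assessment, Primary Outcomes and Statistical Methods, name the end-line between-arm difference in stunting prevalence as the single primary contrast. It is the one that was sized.
- Remove the baseline survey from the primary outcome definition.
- Keep the comparison of change as a labelled sensitivity analysis, and state that it was not powered at 80%.
- Adjustment for subdistrict baseline stunting prevalence may be a prespecified supporting analysis. It should not be required or presented as a power gain.

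The cost is wording in three sections. No data beyond the two surveys are needed, and the sample size calculation is unchanged.
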